### Statistical analysis

#### Power calculations and sample size

Power calculations are based on a standard deviation of 11 mmHg for ambulatory systolic BP and 7 mmHg for ambulatory diastolic BP. A sample size of 28 in each stratum of aldosterone: renin ratio would give 80% power to detect a 6 mmHg difference in ambulatory systolic BP and 4 mmHg difference in diastolic BP between spironolactone and bendroflumethiazide treatments. However, we are interested in detecting differences in BP changes comparing the low-ratio and high-ratio arms. We therefore need to randomise 54 subjects into each arm to detect a 6/4 mmHg difference in BP at the α = p < 0.05 (two-sided). Therefore, allowing for dropouts, a sample size of 60 in each arm or 120 subjects in total are required. A multivariate analysis to investigate the effect of age and other characteristics on the effects of Spironolactone is also planned.

#### Analyses

For each outcome the measurement from the spironolactone treatment period will be subtracted from that of the bendroflumethiazide treatment period. Therefore each person has an estimated "treatment effect". The mean difference, between the treatment effects in the high ratio group and those in the low ratio group, will be compared by t-tests and 95% confidence intervals. There may be some secondary Normal Linear Models that also examine other factors, which may also be considered to be confounders, as this is a non-randomised comparison.

The second analysis will be by conventional crossover analyses of the efficacy of spironolactone (in the high-ratio sub-group only). These analyses will be carried out by Normal Linear Models, that include parameters for patient, period and treatment. In the event that a variable is not normally distributed then the within-patient treatment differences will be calculated and then analysed by either t-tests or Wilcoxon tests.

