#### Uncontrolled blood pressure

If blood pressure is uncontrolled investigators may use their discretion and add further antihypertensive medication in the following order of preference: alpha-blockers, centrally acting drugs, calcium channel blockers, cardio-selective beta blockers and (exceptionally) ACE inhibitors and angiotensin receptor blockers. A log of all medication taken during the study is kept for each subject.

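### The main between-stratum t-test leaves out treatment period, which the plan's own second analysis fits; adding sequence costs one degree of freedom and protects power if a period effect exists

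*Protocol article*

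**What the plan says.** All of this is in the protocol article, Statistical analysis, under Analyses.

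- **Analysed variable.** For each outcome, "the measurement from the spironolactone treatment period will be subtracted from that of the bendroflumethiazide treatment period". The order in which the patient took the drugs plays no part.
- **First analysis.** "The mean difference, between the treatment effects in the high ratio group and those in the low ratio group, will be compared by t-tests", with 95% confidence intervals. The article does not call this the primary analysis. It is so in substance: it answers the primary objective, it is the contrast for which the sample-size section asks for 54 per stratum, and the analysis that follows is called the second.
- **Second analysis.** A crossover analysis confined to the high-ratio subgroup, using "Normal Linear Models, that include parameters for patient, period and treatment". It does not estimate the contrast between strata.
- **Fallback for non-normal variables.** "the within-patient treatment differences will be calculated and then analysed by either t-tests or Wilcoxon tests". Period drops out again.
- **Further models.** "There may be some secondary Normal Linear Models that also examine other factors". They are optional and secondary, and period is not named.

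Under Study design, treatment order comes from a computer-generated list stratified by ratio. The article does not say whether the two sequences are balanced within a stratum.

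**The concern.** In a two-period crossover, a period effect enters each patient's drug difference with a sign that depends on the sequence. Two consequences follow if the analysis ignores sequence.

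First, the differences spread more widely than the drugs and patients alone would make them. The t-test counts that extra spread as noise.

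Second, if one stratum has relatively more patients on one sequence than the other stratum has, part of the period effect stays in the estimated contrast.

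The sequence is known for every patient, and the plan already fits period in its supporting analysis. The test on which the trial was sized is the one left unadjusted. What is at stake is mainly power and, for a particular realised split, the accuracy of the estimate.

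**Working it through.** **Inputs.** From the sample-size section: SD 11 mmHg (systolic), target 6 mmHg, two-sided 5%, 54 per stratum, 60 after dropout. The 80% power is stated for 28 per stratum and is taken to carry over to 54. Assumptions: 11 is the SD of the within-patient difference and is free of period variation; the period effect p (period 2 minus period 1) is common to both strata and lies between 0 and 8 mmHg.

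**The plan's own figure.** n per stratum = 2 × (1.96 + 0.84)² × 11² / 6² = 52.8, so 53 by the normal formula. The noncentral-t power at 54 per stratum is 80.2%. Dropout: 54 / 0.90 = 60. The stated sample size is reproduced.

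**How p enters.** The difference is bendroflumethiazide minus spironolactone. A patient given spironolactone first contributes +p; a patient given bendroflumethiazide first contributes −p. With sequences 1:1, the variance of the difference is 11² + p².

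**Power of the unadjusted t-test, 54 per stratum.**

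| p (mmHg, assumed) | SD = √(121 + p²) | Power |
|---|---|---|
| 0 | 11.00 | 80.2% |
| 1 | 11.05 | 79.9% |
| 2 | 11.18 | 78.9% |
| 3 | 11.40 | 77.3% |
| 5 | 12.08 | 72.5% |
| 8 | 13.60 | 62.2% |

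Simulation with sequences fixed at exactly 27:27 in both strata gives slightly more: about 78% at p = 3, 74% at p = 5 and 65% at p = 8. In that case the period terms cancel in the means and inflate only the estimated variance. For the same reason the test is then conservative: simulated type I error is about 4.2% at p = 3 and 3.1% at p = 5.

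**Shift in the estimate.** Within a stratum of n analysed patients, let the imbalance be (number spironolactone first − number bendroflumethiazide first) / n. The contrast moves by p × (imbalance in high stratum − imbalance in low stratum).

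- 30:24 against 25:29, p = 5: 5 × (6/54 − (−4/54)) = 5 × 10/54 = 0.93 mmHg, or 15% of the 6 mmHg target.
- 30:24 against 24:30, p = 5: 5 × 12/54 = 1.11 mmHg. Simulated power is then 88% or 55%, depending on the direction of the imbalance.
- 30:24 in both strata: zero.

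**Type I error under unequal splits (simulation).** At p = 5 it is 4.7% to 4.8% for 30:24 against 25:29 and about 5.5% for 30:24 against 24:30. Averaged over simple randomisation it is about 5% at p = 3, 5 and 8.

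**With sequence in the model.** For p of 0, 3, 5 and 8 mmHg and every split simulated, power is 79% to 80%, the mean estimate is about 6.0 mmHg and type I error is about 5%.

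**The case against.** The strongest case on the other side is that the test is valid as written. Order is randomised within strata, so the expected bias is zero. A common period effect cancels when both strata have the same imbalance, and with balanced sequences the test errs on the cautious side. All of that stands.

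Three stronger readings are tempting, and the documents do not support them.

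- **Inflated type I error.** A reader might infer that dropout pushes the error well above 5%. If allocation is 30:30 within a stratum (an assumption), losing the planned 6 of 60 leaves at worst 30:24, where the error is about 5.5% at p = 5. Clear inflation needs splits such as 32:22 against 22:32, which this loss cannot produce. If the list is not balanced, such splits can arise by chance, but the error rate over randomisation is still about 5%.
- **A period effect is likely.** A reader might point to entry on raised blood pressure, or to the rule that "investigators may use their discretion and add further antihypertensive medication". Regression to the mean after screening falls mainly before the end of period 1, and the endpoint compares the ends of the two periods. The article does not say that added drugs continue into period 2, and it gives no rate of such additions. A period effect is possible, but its size is unknown.
- **Any imbalance biases the contrast.** Only an imbalance that differs between strata does so, given a common period effect.

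Two further points temper the size. If the SD of 11 came from differences not adjusted for period, planned power already allows for it, and adjustment would raise power above 80%. At 1 to 2 mmHg the loss is little more than one percentage point at most.

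The condensed format does not answer the point. The method for the main contrast is stated, and period is named in one analysis and absent from the other. The optional models do not change the main test.

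**Conclusion.** The point holds as an avoidable inefficiency in the main test and should be fixed. The test is not invalid, and the sample size is not wrong.

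Under the planning figures, ignoring period costs about 3 percentage points of power at a period effect of 3 mmHg, 8 at 5 mmHg and 18 at 8 mmHg, and almost nothing at 1 mmHg. An estimate shift of about 1 mmHg is possible at 5 mmHg when the strata have opposite imbalances. That shift is conditional on the realised split.

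These sizes rest on an assumed period effect, on SD 11 being free of period variation and, for the limit on type I error in a given split, on sequences starting balanced within strata with no more than the planned dropout.

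**What to change.** Make the main analysis a linear model of the within-patient difference on ratio stratum and sequence, and report the stratum coefficient with its 95% CI. An equivalent is one mixed model with patient, period, treatment and treatment-by-stratum (with a stratum term if patient is random), reporting the treatment-by-stratum coefficient.

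Keep period in the fallback for non-normal variables as well. For example, take each patient's period 1 minus period 2 difference and compare the two sequence groups by a Wilcoxon rank-sum test, in place of a test on the raw drug differences.

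Fix this before unblinding, so that the choice to adjust cannot be questioned later. The cost is a sentence or two in the Analyses section and one residual degree of freedom (105 instead of 106 with 54 per stratum). No new data and no change in sample size are needed.

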**Methods/design:**

The study is a double-blind, randomised, crossover, controlled trial that will randomise 120 hypertensive subjects to 12 weeks treatment with spironolactone 50 mg once daily and 12 weeks treatment with bendroflumethiazide 2.5 mg once daily. The 2 treatment periods are separated by a 2-week washout period. Randomisation is stratified by aldosterone: renin ratio to include equal numbers of subjects with high and low aldosterone: renin ratios.

Primary Objective – To test the hypothesis that the aldosterone: renin ratio predicts the antihypertensive response to spironolactone, specifically that the effect of spironolactone 50 mg is greater than that of bendroflumethiazide 2.5 mg in hypertensive subjects with high aldosterone: renin ratios.

Secondary Objectives – To determine whether bendroflumethiazide induces adverse metabolic abnormalities, especially in subjects with high aldosterone: renin ratios and if baseline renin measurement predicts the antihypertensive response to spironolactone and/or bendrofluazide

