#### Secondary endpoints

Secondary endpoints include the differences between the following measurements taken at the end of each 12-week treatment period

• Mean 24 hour diastolic ambulatory blood pressure

• Mean daytime ambulatory blood pressure

• Mean night time ambulatory blood pressure

• Mean clinic blood pressure defined as mean of mean clinic BPs on both penultimate and final days of treatment periods

• Clinical biochemistry measurements of plasma potassium (K^+^), magnesium (Mg^2+^), creatinine, triglycerides, cholesterol and HDL cholesterol

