### QT dispersion

QT dispersion is measured from routine ECGs recorded at baseline and at the end of each treatment period. Spironolactone has been shown to reduce QT dispersion in chronic heart failure[23] and it is of interest to investigate whether this is also the case in hypertension and whether such an effect is more prominent in subjects with a high aldosterone: renin ratio.

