### Plasma PIIINP (Procollagen Type III N-terminal Peptide)

Plasma PIIINP is a marker for collagen formation in the heart and spironolactone has been found to reduce PIIINP in heart failure[26]. We wish to examine whether if this is also the case in hypertension.

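### The test set for every outcome contrasts the ratio strata, so no stated analysis compares the two drugs metabolically in all patients

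*Protocol article*

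**What the plan says.** The secondary objective (Protocol article, Abstract, Methods/design) is "To determine whether bendroflumethiazide induces adverse metabolic abnormalities, especially in subjects with high aldosterone: renin ratios". The Secondary endpoints section lists the relevant measures, starting "Clinical biochemistry measurements of plasma potassium" and continuing with magnesium, creatinine, triglycerides, cholesterol and HDL cholesterol. It defines them as within-trial drug comparisons: "Secondary endpoints include the differences between the following measurements taken at the end of each 12-week treatment period".

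The Analyses section then sets out two analyses.

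- **First, for every outcome.** "For each outcome the measurement from the spironolactone treatment period will be subtracted from that of the bendroflumethiazide treatment period". The test named for these differences is the comparison between strata: "The mean difference, between the treatment effects in the high ratio group and those in the low ratio group, will be compared by t-tests". The same paragraph acknowledges that this comparison is not a randomised one.
- **Second, a drug comparison.** This is described as "conventional crossover analyses of the efficacy of spironolactone (in the high-ratio sub-group only"), using a linear model with patient, period and treatment terms.

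The section also mentions possible further linear models that look at other factors or confounders. Power calculations and sample size mentions a multivariate analysis of age and other characteristics. Neither is described as an overall comparison of the drugs.

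**The concern.** The objective holds two questions. *Whether* there is a metabolic effect concerns the drug difference in the study patients. *Especially* concerns how that difference varies with the ratio. The test fixed for every outcome addresses only the second question.

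Suppose potassium or cholesterol differs between the drugs by the same amount in both strata. The contrast then has expectation zero, however large the difference. A non-significant contrast could be reported as no metabolic finding although the drugs differ in everyone.

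The second analysis would show such a difference, but its wording leaves it unclear whether biochemistry is covered, and it leaves out the low-ratio half. Yet the within-patient drug difference is the comparison that randomisation protects. The sample-size section also quotes power for it in each stratum, while the Analyses section never tests it in the low-ratio stratum.

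**Working it through.** **Inputs.** Power calculations and sample size gives SD 11 mmHg and a 6 mmHg difference for systolic pressure, 28 per stratum for the drug difference, 54 per stratum for the contrast, 80% power and two-sided 5% (60 per stratum after allowing for dropout). The documents give no SD or expected effect for any biochemical measure. Effects *d* are therefore in units of the SD of the within-patient difference, and *d* = 0.2 to 0.5 is an assumption.

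**The plan's own figures.**

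- Drug difference within a stratum: n = (1.960 + 0.842)² × (11/6)² = 7.85 × 3.36 = 26.4, so 27. The exact t-test power at 28 is 79.5%.
- Contrast between strata: n = 2 × 7.85 × 3.36 = 52.8, so 53 per stratum. The exact t-test power at 54 is 80.2%.

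Both reproduce the stated 28 and 54 closely, with 11 mmHg read as the SD of the within-patient difference. The planned size thus rests on the contrast.

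**What each analysis estimates.** Let δH and δL be the mean drug differences (bendroflumethiazide minus spironolactone) in the high- and low-ratio strata.

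- Stated test for every outcome: δH − δL. If δH = δL, this is exactly 0. No numerical assumption is needed.
- Stated drug comparison: δH only.
- Not stated: (δH + δL)/2, the average over both strata.

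**Precision with 54 completers per stratum** (equal SD in both strata).

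- Averaged over both strata: 1/√108 = 0.096 SD.
- High-ratio stratum only: 1/√54 = 0.136 SD.
- Contrast: √(2/54) = 0.192 SD.

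The effects detectable with 80% power are 0.27, 0.39 and 0.54 SD respectively.

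**Power for an effect equal in both strata** (exact noncentral t).

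| Common effect *d* (SD) | Contrast, 54 v 54 | High-ratio only, n = 54 | All patients, n = 108 |
|---|---|---|---|
| 0.2 | 5% | 30% | 54% |
| 0.3 | 5% | 58% | 87% |
| 0.4 | 5% | 82% | 98.5% |
| 0.5 | 5% | 95% | 99.9% |

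The 5% is simply the type I error rate. A simulation of 20,000 trials agrees: at *d* = 0.3 the mean contrast was −0.001 with 4.8% rejections, and at *d* = 0.5 it was 0.000 with 4.9%. The high-ratio and all-patient rejection rates at *d* = 0.3 were 58.6% and 87.3%.

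**The case against.** **The high-ratio analysis may cover biochemistry.** It is written in the plural and has a fallback for variables that are not normally distributed, which suits several outcomes better than one blood pressure endpoint. If biochemistry is covered, a large common difference would probably be found: 82% power at 0.4 SD and 95% at 0.5 SD. This stands. A reader might infer that a common metabolic harm cancels altogether and that the objective must return a null answer. The document does not support that, because cancellation is a property of the contrast alone.

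**There is no placebo period.** The objective asks what bendroflumethiazide induces, but any difference between the periods may come from either drug. The Hypokalaemia/hyperkalaemia section itself provides for potassium moving in both directions on study medication. This also stands, and it limits what an all-patient comparison can claim.

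**This is a condensed article.** Models for secondary outcomes are often left to a fuller document, and the within-stratum means must be computed for the stated t-test anyway. This stands in part. The point, however, concerns what the text fixes: it names a test for each outcome, and that test does not match the endpoint as a drug difference or the *whether* part of the objective.

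**The average describes no natural population.** The strata are forced to equal size, although only 15% of unselected patients have a ratio above 750, and patients with ratios between 300 and 750 are not entered. This is fair. It is a reason to label the average and report the strata beside it, not to omit the comparison.

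**Sub-studies.** It is tempting to extend the point to them. QT dispersion says "it is of interest to investigate whether this is also the case in hypertension and whether such an effect is more prominent in subjects", meaning those whose ratio is high, and the PIIINP section says only "We wish to examine whether if this is also the case in hypertension". But the Substudies section states no analysis, so applying the test for each outcome to it is an inference. Endothelial function is measured in only a subset, so the figures for 54 per stratum do not carry over.

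**Conclusion.** The concern holds in a limited form. For the biochemistry endpoints, the test fixed for every outcome answers only whether the drug difference varies by stratum. The one stated drug comparison is worded as efficacy and confined to the high-ratio stratum. A metabolic difference common to both strata is therefore either untested, or tested with a standard error about 1.4 times what the collected data allow (0.136/0.096). At an assumed 0.3 to 0.4 SD this means 58% to 82% power instead of 87% to 98.5%.

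The loss of a common effect from the contrast is algebraic. The power figures rest on assumed effect sizes, equal SDs in the two strata and 54 completers in each. The primary blood pressure question, which is about the contrast, is not affected.

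**What to change.** For the biochemistry endpoints, state that the crossover model is fitted to all randomised patients with patient, period, treatment and treatment-by-stratum terms. Report, in this order:

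1. the drug difference averaged over the two strata, labelled as a 50:50 mix, with its 95% confidence interval;
2. the drug difference in each stratum;
3. the contrast between strata, kept as the answer to *especially*.

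Describe the averaged result as bendroflumethiazide relative to spironolactone, not as proof that bendroflumethiazide alone induces the change. State also whether the high-ratio crossover analysis covers biochemistry. The same model may be used for sub-study measures recorded in both periods and both strata, with the same caveat about the active comparator.

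The cost is a few sentences of analysis text. It needs no new data or patients and leaves the primary analysis as it is. If the full protocol or analysis plan already contains this comparison, the article only needs to say so.

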
### Rationale for doses of bendroflumethiazide and spironolactone

Previous studies with thiazide diuretics have suggested that the dose-response relationship is shallow. With bendroflumethiazide, the most commonly used thiazide in the UK, 2.5 mg is almost as effective as 5 mg and as a consequence very few physicians use the higher dose. In essential hypertension, a similar dose-response relationship is true for spironolactone but higher doses of spironolactone may reduce BP more in those with high aldosterone: renin ratios. In one sense, the ideal comparison would be between exactly equipotent doses of these two drugs. However, the critical question is whether the efficacy of the usually prescribed doses of these drugs is predicted by the aldosterone: renin ratio. This is the pragmatic question that is relevant to day-to-day clinical practice. In order to test this hypothesis, it is not necessary for the doses employed to be exactly equipotent. For this reason we have chosen 50 mg of spironolactone, to be compared with 2.5 mg of bendroflumethiazide, the most commonly used doses of each drug.

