## Methods/design

### Study design

The study is a double-blind, randomised, crossover, controlled trial that will randomise 120 hypertensive subjects to 12 weeks treatment with spironolactone 50 mg once daily and 12 weeks treatment with bendroflumethiazide 2.5 mg once daily. The 2 treatment periods are separated by a 2-week washout period. Investigators and subjects do not know the order of the treatment periods, which is according to a computer generated randomisation list. Randomisation is stratified by aldosterone: renin ratio to include equal numbers of subjects with high and low aldosterone: renin ratios. This is necessary as in an unselected population, only 15% of subjects will have an aldosterone: renin ratio > 750.

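### The primary objective is specified as spironolactone superiority in high-ratio patients, which does not test prediction; align it with the powered between-strata contrast and fit the crossover model in both strata

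*Protocol article*

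**What the plan says.** The primary objective (Abstract, Methods/design) has two parts. The general part is "To test the hypothesis that the aldosterone: renin ratio predicts the antihypertensive response to spironolactone". It is then narrowed: "specifically that the effect of spironolactone 50 mg is greater than that of bendroflumethiazide 2.5 mg in hypertensive subjects with high aldosterone: renin ratios". The narrowed part makes no comparison with low-ratio patients.

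The rest of the article is built on a different contrast. Under Power calculations and sample size, 28 per stratum is given as enough for drug against drug within a stratum. The authors then say "we are interested in detecting differences in BP changes comparing the low-ratio and high-ratio arms" and raise the number to 54 per stratum, and to 60 with dropouts. Under Analyses, the first comparison is between strata: "The mean difference, between the treatment effects in the high ratio group and those in the low ratio group, will be compared by t-tests".

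The second comparison is "conventional crossover analyses of the efficacy of spironolactone (in the high-ratio sub-group only". It uses a Normal linear model with patient, period and treatment terms. No such model is described for the low-ratio stratum, although the Study design section says "Randomisation is stratified by aldosterone: renin ratio to include equal numbers of subjects with high and low aldosterone: renin ratios".

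**The concern.** Prediction by the ratio means that the spironolactone-minus-bendroflumethiazide effect differs between high-ratio and low-ratio patients. Superiority in high-ratio patients is a separate hypothesis. It can be true when the ratio carries no information, for instance if spironolactone at the trial dose is simply the stronger drug in everyone. As worded, the objective's specific clause and the contrast that sets the sample size are different hypotheses, and the article does not say which one decides the primary question.

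The restriction of the crossover model has its own consequence. The Rationale for study section asks whether ratio-guided treatment would be better than a thiazide for all. To answer that, a reader needs the drug difference in low-ratio patients as well as in high-ratio patients, estimated in the same way.

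**Working it through.** **Inputs.** From Power calculations and sample size: SD 11 mmHg systolic, difference 6 mmHg, two-sided 5%, 28 per stratum at 80% power within a stratum, 54 per stratum between strata, 60 after dropouts. Assumption: 11 mmHg is the SD of the within-patient difference. The article does not say so, but this reading reproduces both 28 and 54.

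**1. The plan's own figures.**
- Within a stratum (paired): n = (11 × 2.802 / 6)² = 26.4 by the normal approximation and 28.4 by the t distribution. Power at 28 is 79.5%.
- Between strata (two-sample): n = 2 × 26.4 = 52.8 per stratum, or 53.7 by t, so 54. Power at 54 is 80.2%.
- Dropouts: 54 / 0.90 = 60 (the 10% is inferred).

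The figures hold, and 54 per stratum is the size for the between-strata contrast.

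**2. A scenario with no prediction.** Suppose spironolactone is better by 6 mmHg in both strata.
- High-ratio test: standard error = 11 / √54 = 1.497; 6 / 1.497 = 4.01; 4.01 − 1.96 = 2.05, a power of about 98%. The noncentral t gives 97.6% at 54 and 98.6% at 60. With a uniform advantage of 4 mmHg it is 74.7%, and with 3 mmHg 50.3%.
- Between-strata test: the true difference is 6 − 6 = 0, so it is significant at its nominal 5%. In 40,000 simulated trials with 54 per stratum it was significant in 4.9%, and in 2.4% in the direction of a larger effect in high-ratio patients.

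**3. If the SD means something else.** If 11 mmHg is the SD of a single measurement and r is the within-patient correlation, the SD of the difference is 11 × √(2(1 − r)). The chance that the high-ratio test is significant under the uniform 6 mmHg advantage (normal approximation, n = 54) is then:

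| r | SD of difference | 6 / (SD / √54) − 1.96 | Probability |
|---|---|---|---|
| 0.7 | 8.5 | 3.21 | 99.9% |
| 0.5 | 11.0 | 2.05 | 98% |
| 0.3 | 13.0 | 1.43 | 92% |
| 0 | 15.6 | 0.87 | 81% |

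The between-strata test stays at 5% throughout.

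**4. What the between-strata difference leaves open.** The article subtracts spironolactone from bendroflumethiazide, so positive values favour spironolactone. A between-strata difference of 6 mmHg arises equally from these pairs (high, low):
- (9, 3): spironolactone better in both strata
- (6, 0): better in high, no difference in low
- (3, −3): each drug better in one stratum
- (0, −6): no difference in high, bendroflumethiazide better in low

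The planned high-ratio model separates some of these. The low-ratio estimate completes the picture. At 54 patients its 95% CI would be about ±1.96 × 1.497 = ±2.9 mmHg, against ±1.96 × 11 × √(2/54) = ±4.1 mmHg for the between-strata difference.

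**The case against.** The strongest reply is that the plan already asks the right question. The general part of the objective is prediction, the sample size was raised for the between-strata contrast, and that contrast is the first analysis listed. All of this stands. A reader might infer that a win in high-ratio patients alone would be taken as proof that the ratio predicts response. The article nowhere says so, and the first-listed test guards against that error at its nominal 5%. Nor is the 97.6% an error rate of the second analysis: in that scenario the drug really is better in high-ratio patients, and the analysis correctly finds it. The figure shows only that the narrowed clause cannot stand in for prediction.

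A reader might also infer an inflated familywise error, 8.3% if either test could support the objective at 5%. The article states no such rule and gives no alpha for the second analysis. Rules on testing order may sit in an analysis plan that is not shown. That claim is not supported.

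The remark in the dose rationale, "it is not necessary for the doses employed to be exactly equipotent", might be read as an oversight. It is not: the sentence refers to the hypothesis about prediction, and a uniform potency advantage cancels in the between-strata contrast. If anything, it is a further reason to make that contrast the stated objective.

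On the low-ratio stratum, the first analysis necessarily produces a mean treatment effect in each group, and stratified randomisation should largely balance period effects. So a crude low-ratio estimate will exist. What is lacking is the period-adjusted estimate and a commitment to report it beside the high-ratio one.

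**Conclusion.** The concern holds as a mismatch in the wording of the objective, together with one needlessly narrow analysis. The narrowed clause would be met about 98% of the time under a uniform 6 mmHg advantage with 54 patients and an SD of 11 mmHg for the within-patient difference (81% to 99.9% over the correlations shown), although the ratio would then predict nothing. The sample size and the first-listed analysis target the correct contrast and need no change. The low-ratio restriction matters because the between-strata difference alone does not show which drug is better in low-ratio patients. If spironolactone were better in both strata, the ratio could still predict the size of the advantage, but it would not change which drug lowers blood pressure more. A reader needs both estimates to tell these cases apart.

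**What to change.** 1. Reword the primary objective so that its specific hypothesis is the difference between high-ratio and low-ratio patients in the spironolactone-versus-bendroflumethiazide effect on 24-hour systolic pressure.
2. State under Analyses that the first-listed comparison decides the primary objective and that superiority in high-ratio patients is supportive.
3. Replace the restriction of the crossover model to the high-ratio sub-group with a model fitted in each stratum. Report both period-adjusted drug differences with 95% CIs beside the between-strata difference.

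The cost is a few sentences. No extra patients, visits or measurements are needed, and the sample size stands. The one small downside is that a win in high-ratio patients alone would no longer count as meeting the primary objective.
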